### 8.3 STATISTICAL METHODS TO BE UNDERTAKEN

No censoring will be used for length of hospital stay. The primary outcome will be analyzed using Student's t-test on the log transformed LOS data in hours. Secondary outcomes will be analysed using parametric or non-parametric tests according to the type of data, whether the data is skewed, and whether repeated measures are used. For secondary endpoints, significance will be defined as  $p < 0.01$  to reduce the risk of Type 1 error.

## 9. STORAGE OF BLOOD AND TISSUE SAMPLES

### 9.1 DETAILS OF WHERE SAMPLES WILL BE STORED, AND THE TYPE OF CONSENT FOR FUTURE USE OF SAMPLES

N/A

## **10. DATA SECURITY & HANDLING**

### **10.1 DETAILS OF WHERE RECORDS WILL BE KEPT & HOW LONG WILL THEY BE STORED**

Paper records will be stored in a locked filing cabinet, in a locked room in the Department of Surgery, University of Melbourne. Electronic data are stored on password protected databases, available only to researchers involved in the study.

All paper records used during the study are kept after the project has been completed for a minimum of 5 years, and will be disposed of via shredding of all paper records, and deletion from databanks.

### **10.2 CONFIDENTIALITY AND SECURITY**

Only HREC authorised researchers who are involved in data collection and entry into the database will have access to the information. There are no separate student supervisors who are not associate investigators. Access to the information is provided by the Chief Investigator using login and password process.

Information will remain at the University of Melbourne. If the chief/principal investigator ceases to be engaged at the current organisation the principal investigator will inform the HREC that they will no longer be part of the study. Responsibility of the project will be handed over to an associate researcher working on the study already. HREC will be informed of relevant changes made.

No identifiable information will be used in any publication or presentation, and only group data will be published.

### **10.3 ANCILLARY DATA**

Ultrasound images are stored on a password protected server and only accessible to the researchers.

## 11. APPENDIX

### List of Attachments included:

| Document Name           | Version Number | Date (e.g., 18 January 2012) |
|-------------------------|----------------|------------------------------|
| CRF                     | 1              | 20 May 2018                  |
| iHeart-iLung-veins form | 1              | 28 May 2018                  |
|                         |                |                              |

## **Statistical analysis plan -IMFCU study**

Statistical analysis will be performed using the software SPSS version 27 (Statistical Package for the Social Sciences).

Distribution of demographic and baseline characteristics between groups will be analysed using Fisher test for categorical data and Student's t-test for ordinary data.

The primary outcome, length of hospital stay in hours, will be analysed using Student's t-test on log-transformed data to normalize skewed data and following an intention-to-treat approach. A cut-off of 30 days will be applied to avoid the effect of excessively extended hospital stays. Significance was defined as  $p < 0.05$ . For patients who died in the hospital, death will be treated as hospital discharge for the primary analysis as the unpublished mortality rate for patients admitted to internal medicine wards at the Royal Melbourne Hospital is low (2.7%). Patients with missing data will not be included in the primary statistical analysis.

Because the introduction of Focused Clinical Ultrasound (FCU) was new to the internal medicine unit, we hypothesised that there would be a lead-in period where the FCU findings may not be accepted by the treating team, whereas as the physicians became more familiar with FCU, the finding would be more trusted and more likely to be acted upon. A sensitivity analysis will be performed on outcomes to compare the first half versus the second half of the participants.

The primary outcome will be analysed in pre-defined subgroups that we suspect a stronger effect of FCU: older than 75 years old, history of chronic heart failure, history of chronic obstructive pulmonary disease and patients with multiple comorbidities.

Secondary outcomes will be analysed using parametric or non-parametric tests according to the type of data. All estimates will be reported with 95% confidence intervals.

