| Safety considerations:      | The focused cardiac, lung and vein ultrasound is non-invasive and does not present risk to the patient                                                                                                                                                                                                                                                                                                                                                                                                                                                                                                                                                                                                                                                                                                                               |
| Statistical Methods:        | 
The outcome of interest, hospital length of stay (LOS), is expected to be skewed and hence will be log transformed for the purposes of analysis. Control data were available for Q4 2017, with a mean log based 10 LOS of 2.01 (equivalent to 103 hours on the original scale) and a standard deviation of 0.36. In this study censoring will not be applied to the LOS. The primary outcome will be tested using Student t-test on the log-transformed LOS data.
 
In order to detect a clinically important reduction in LOS of 24 hours for the ultrasound group, based on the expected control value above and a common standard deviation on the log scale, power of 0.8 and size 0.05, 122 participants are required in each of the two treatment groups, which will be rounded up to a total of 250 participants.
 |

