### 8.2 POWER CALCULATIONS

The outcome of interest, hospital length of stay (LOS), is expected to be skewed and hence will be log transformed for the purposes of analysis. Control data was available from 2017, with a mean log based 10 LOS of 2.01 (equivalent to 103 hours on the original scale) and a standard deviation of 0.36.

In order to detect a clinically important reduction in LOS of  $\geq 24$  hours for the ultrasound group, based on the expected control value above and a common standard deviation on the log scale, power of 0.8 and size 0.05, 122 patients are required in each of the two treatment groups, which will be rounded up to a total sample size of 250 participants.

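### The plan hypothesises that the FCU effect grows after a lead-in period and is stronger in four subgroups, but does not specify estimating any difference in FCU effect.

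*Protocol*

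**What the plan says.** The section headed Statistical analysis plan - IMFCU study, bound at the end of the Protocol, sets out two hypotheses about a varying effect.

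- **Lead-in period.** FCU was new to the unit, and the plan expects that "as the physicians became more familiar with FCU, the finding would be more trusted and more likely to be acted upon". The analysis that follows is: "A sensitivity analysis will be performed on outcomes to compare the first half versus the second half of the participants".
- **Subgroups.** "The primary outcome will be analysed in pre-defined subgroups that we suspect a stronger effect of FCU". The four named are age over 75, chronic heart failure, chronic obstructive pulmonary disease, and multiple comorbidities.

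The primary outcome, length of stay (LOS), "will be analysed using Student's t-test on log-transformed data to normalize skewed data and following an intention-to-treat approach", with significance at 0.05. The other inferential methods named are Fisher's test and unspecified parametric or non-parametric tests. The section promises 95% confidence intervals for all estimates. Neither it nor Protocol section 8 mentions an interaction term, a test of heterogeneity, or an estimate of the difference between two FCU effects.

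**The concern.** A growing effect and a stronger effect are both statements that the arm difference changes across levels of another factor. Only a comparison of arm differences addresses them. The half-versus-half sentence can be taken in two unhelpful ways, each with its own problem.

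- **Arms pooled.** First-half participants are compared with second-half participants. Season, case mix and bed pressure then enter the comparison directly.
- **Arms compared separately within each half.** Each contrast is a valid randomised one. The step from significant here and not there to a different effect is not valid.

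The subgroup sentence carries the second problem. At stake is a report of a learning curve, or of a subgroup that benefits more, when the effect is the same throughout. The main conclusion of the trial is not at stake.

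**Working it through.** **Inputs.** Section 8.2 gives control data "with a mean log based 10 LOS of 2.01 (equivalent to 103 hours on the original scale) and a standard deviation of 0.36". The synopsis sets the target: "In order to detect a clinically important reduction in LOS of 24 hours for the ultrasound group". Section 8.2 states "power of 0.8 and size 0.05, 122 patients are required in each of the two treatment groups". The planned total in the same section is 250, that is, 125 per arm and about 62.5 per arm in each half.

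**Effect on the log10 scale.** log10(103/79) = 0.1152. Using 10^2.01 = 102.3 h instead, log10(102.3/78.3) = 0.1161. Both are carried as a range where they differ.

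**The plan's own figure.** n per arm = 2 × 0.36² × (z_alpha + z_0.80)² / effect². A one-sided 0.05 gives 119 to 121 (120 to 122 with the t distribution), which matches 122. A two-sided 0.05 gives 151 to 154. The documents do not state sidedness. Two-sided 0.05 is assumed below, and the one-sided result is shown where it matters.

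**Reading 1: arms pooled.** If the effect moves from nil in the first half to the full 24 h in the second, the pooled mean shifts by half the effect: 0.1161/2 = 0.058. The SE is 0.36 × sqrt(2/125) = 0.0455, so power is about 25%. A secular LOS change of 0.058 in both arms would look identical.

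**Reading 2: separate tests in each half, same true effect in both.**
- SE of the effect within a half = 0.36 × sqrt(2/62.5) = 0.0644.
- Power per half: 0.1152/0.0644 = 1.79 and 0.1161/0.0644 = 1.80, giving 43% to 44%.
- Exactly one half significant: 2 × 0.437 × 0.563 = 0.492. A simulation of 40,000 trials with 62 per arm per half gave 0.492.
- Second half only: 0.437 × 0.563 = 0.246 (0.245 with the smaller effect). This is the pattern that the lead-in hypothesis predicts.
- One-sided 0.05: power per half is 56%, and 2 × 0.563 × 0.437 = 0.492, so the discordance is unchanged.
- In the same simulation the interaction test rejected in 5.0% of trials.

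**Reading 2 with no effect.** Exactly one half significant in either direction: 2 × 0.05 × 0.95 = 9.5%. Second half only and favouring FCU: 0.025 × 0.95 = 2.4%.

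**Subgroups, same true effect throughout.** Prevalences are not given, so 20% to 50% is assumed. Power within the subgroup is 21% to 44%. Subgroup and complement disagree on significance in 57% to 49% of trials. The subgroup alone is significant in 8% to 25%.

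**Subgroups, no effect.** 1 − 0.95^4 = 18.5% for any false positive in either direction, if independent. For a false benefit only, 1 − 0.975^4 = 9.6%. The four subgroups share patients, so these are upper figures. The 0.01 threshold in section 8.3 covers secondary endpoints, not subgroup analyses of the primary outcome.

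**What an interaction test can do.** SE of the difference in effects = 0.36 × sqrt(4/62.5) = 0.0911. For nil in one half and the full effect in the other, 0.1152/0.0911 = 1.26 and 0.1161/0.0911 = 1.27, so power is 24% to 25%. For subgroups of 20% to 50% it is 17% to 25%. Power of 80% for that difference between halves would need 4 × 0.36² × (1.96 + 0.84)² / 0.1161² = 302 per arm per half, or 1,208 in total.

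**The case against.** The half-versus-half sentence follows directly on a hypothesis about FCU findings being acted upon. Comparing the FCU effect between halves is therefore a natural reading, and that is an interaction. Nothing excludes it, and nothing says that a claim will rest on discordant p-values. This stands, so the point is unspecified wording, not a decision against interactions.

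A reader might infer that the plan cannot show a differing effect. The documents do not support that. If arm effects are reported by half with the promised 95% intervals, the halves are independent and the difference and its interval can be derived. The answer is weaker for subgroups, because the plan does not say that the complements will be reported.

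A reader might also combine the two criticisms of the half analysis. They belong to different readings. Confounding by calendar time applies only if arms are pooled. Within each half, the permuted blocks of 4, 6 and 8 in section 5.3 keep the arms nearly balanced.

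The stakes are limited too. The half comparison is called a sensitivity analysis, the subgroups are pre-defined, and the proper test has low power. That lowers the weight of the point but leaves it in place: a weak test with a stated interval is still preferable to a rule that misleads about half the time.

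**Conclusion.** The point holds as a gap in specification for two secondary questions. The plan states two hypotheses of effect modification and specifies no estimate of a difference in FCU effect.

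On the separate-tests reading, a constant 24 h effect makes exactly one half significant in about 49% of trials and only the second half in about 24.5%. These figures rest on SD 0.36, 250 participants split equally by arm and half, and two-sided 0.05. They also require a real and constant effect. It would be wrong to infer a one-in-four risk of an apparent learning curve when FCU does nothing; that risk is about 2.4% for a pattern favouring FCU. The 18.5% for subgroups is an upper figure that counts both directions.

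The primary t-test, the sample size and the main conclusion are unaffected. The change should be made, but the trial does not depend on it.

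**What to change.** Replace the two sentences in the statistical analysis plan section with the following.

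- For log10 LOS, fit arm, factor and arm-by-factor interaction in all randomised participants: once for enrolment half (or enrolment order as a continuous term), and once for each of the four subgroups against its complement. The comorbidity subgroup needs a definition that can be coded.
- The half comparison covers outcomes in the plural, so use the corresponding arm-by-half model for each other outcome compared between arms.
- Report the interaction estimate with its 95% CI, and the FCU effect in each level with its CI.
- Label all of these exploratory and state the low interaction power. Five interaction tests on LOS still carry up to 1 − 0.95^5 = 22.6% chance of at least one false positive (independence assumed).
- State that no claim about a period or subgroup will rest on a p-value from within one level.

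The cost is wording and a few extra regression models on data already collected. The downside is fewer subgroup statements that can be called significant.

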### **1) Health costs:**

If the health costs data is skewed, it will be log-transformed to normalise its distribution and analysed using Student's t-test.

- 2) 30-day readmission data will be presented as dichotomic data and analysed using Fisher exact test.
- 3) The impact of FCU on the diagnosis and management will be reported in the intervention group only describing the number and proportion of participants.

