| Secondary Objectives | Time and cost analysis on major investigations and diagnoses prior to establishment of the definitive diagnosis

Health economic analysis                                                                                                                                                                                                                                                                  |
| Inclusion Criteria:  | Participants will be considered for inclusion if they meet all of the following criteria: 
 
• Adult participants (<math>\geq</math>18 years) with a cardiopulmonary diagnosis.
 
• Admitted to a general medical unit at the Royal Melbourne Hospital
 
• Able to provide informed consent
 
• Expected to remain in hospital >24 hours.
 
 |
| Exclusion Criteria:  | Participants will be excluded if they meet any of the following criteria: 
 
• admitted >24 hours
 
• admitted for social rather than medical reasons
 
                                                                                                                                                                                                   |

**Study Name:** A randomized trial of focused cardiac, lung, and femoral and popliteal vein ultrasound on the length of stay in internal medicine admissions with a cardiopulmonary diagnosis – the IMFCU 1 study

**Protocol Number:** 2018.200

**Version & date:** version 1 dated 20 May 2018

Page 5 of 18

|                             |                                                                                                                                                                                                                                                                                                                                                                                                                                                                                                                                                                                                                                                                                                                                                                                                                                      |

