| Subgroups:                  | 
Standard care: no focused ultrasound is performed. Diagnosis and management decisions will be recorded prospectively.
 
Intervention group: Within 24 hours of admission to hospital, the researcher will perform a focused cardiac, lung, and femoral and popliteal vein ultrasound. The findings will be revealed to the medical team after they have completed a diagnosis and management form. Thereafter, all management is directed by the treating medical team and specifically, the intervention will not provide any management guidelines.
                                                                                                                                                                                                                                                                    |

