### 4.2 STUDY AIMS

To identify whether focused cardiac, lung and femoral & popliteal ultrasound to clinical evaluation:

- a. Reduced length of stay
- b. Shortens the time to definitive diagnosis
- c. Reduced the number of imaging or pathology tests performed prior to the definitive diagnosis is made
- d. Identifies >10% of new significant heart or lung pathology
- e. Is cost effective

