### 4.3 OUTCOME MEASURES

- A. Primary outcome: length of stay measured in hours from the time of admission to the medical unit until discharge from the hospital
- B. Secondary outcomes
  - a. Time from admission to establishment of the definitive diagnosis (hours)
  - b. The frequency and type of new cardiopulmonary diagnoses that were not diagnosed prior to performance of the FCU and Lung ultrasound
  - c. The number and type of imaging and pathology investigations performed prior to establishment of the definitive diagnosis.
  - d. Cost will be based on bed stay and investigation costs for the Royal Melbourne Hospital
  - e. The proportion of participants where imaging cannot be obtained.

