#### 2. Cohort:

---

**Study Name:** A randomized trial of focused cardiac, lung, and femoral and popliteal vein ultrasound on the length of stay in internal medicine admissions with a cardiopulmonary diagnosis – the IMFCU 1 study

**Protocol Number:** 2018.200

**Version & date:** version 1 dated 20 May 2018

Page 10 of 18

- a. Adult participants  $\geq 18$  years will be included if they can provide informed consent and are admitted to an internal medicine unit at the Royal Melbourne Hospital with a cardiopulmonary diagnosis and are expected to remain in hospital  $> 24$  hours.
  - b. Exclusion: Participants will be excluded if they have already been admitted  $> 24$  hours, are admitted for social rather than medical reasons, are unable to provide consent, are on contact or respiratory isolation, or have received a transthoracic echocardiogram within 4 weeks prior to admission, or a CT chest scan during the admission process prior to enrolment.
- 3. Location: Single-centre at the Royal Melbourne Hospital
- 4. The primary outcome will identify whether the ultrasound examinations leads to a meaningful reduction in length of stay. The secondary outcomes are designed to identify mechanisms to explain an effect if observed, such as the incidence of new diagnoses which were missed by clinical evaluation and the number of tests required prior to the definitive diagnosis being established.
- 5. Measurements – all measurements are re-identifiable
  - a. Demographic information including gender, age, height and weight, prior medical conditions, medications, admission diagnosis
  - b. Diagnosis information including the initial differential diagnosis, alternative diagnosis and the definitive diagnosis.
  - c. Times including hospital length of stay, time to definitive diagnosis
  - d. Investigations performed (type and number of tests)
    - i. Imaging such as X-ray, CT, MRI, nuclear medicine and ultrasound including echocardiography
    - ii. Pathology tests such as blood tests, urine tests, bacterial cultures or viral swabs.
  - e. Cardiac, lung and vein pathology identified on the focused cardiac, lung, and femoral and popliteal vein ultrasound (intervention group only)
- 6. Data collection and handling
  - a. Data will be collected through interview and extracted from hospital records.

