## 5.2 STANDARD CARE AND ADDITIONAL TO STANDARD CARE PROCEDURES

| Standard Care Procedures            |                                        |               | Additional To Standard Care                                     |                                          |               |
|-------------------------------------|----------------------------------------|---------------|-----------------------------------------------------------------|------------------------------------------|---------------|
| Procedure                           | Time/Visit                             | Dosage/Volume | Procedure                                                       | Time/Visit                               | Dosage/Volume |
| Clinical Evaluation by medical team | Daily until discharge                  | NA            | Focused Cardiac, Lung and femoral and popliteal vein Ultrasound | Within 24 hours of admission to hospital | NA            |
| Investigations                      | As determined by treating medical team | NA            |                                                                 |                                          |               |
|                                     |                                        |               |                                                                 |                                          |               |

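### The planned t-test on log-transformed costs compares geometric means, whereas the cost-effectiveness aim needs the difference in arithmetic mean cost per patient

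*Protocol*

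**What the plan says.** The statistical analysis plan at the end of the protocol document, item 1, fixes the method: "If the health costs data is skewed, it will be log-transformed to normalise its distribution", and the comparison is then by Student's t-test. It names no back-transformation, mean cost difference or incremental measure. Its general text promises 95% confidence intervals for all estimates.

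The purpose is set elsewhere. The synopsis lists "Health economic analysis" among the secondary objectives, and aim (e) in Section 4.2 asks whether the ultrasound "Is cost effective".

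Section 4.3 defines the content of the cost: "Cost will be based on bed stay and investigation costs for the Royal Melbourne Hospital". Section 8.3 sets significance for secondary endpoints at p < 0.01.

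**The concern.** A health economic question is about total spending: mean cost per patient times the number of patients. Only the arithmetic mean has that property. A t-test on log costs compares means of log cost, which back-transform to geometric means. If the spread of log cost differs between arms, the ratio of geometric means and the ratio of mean costs differ too. The test can then signal a difference when mean costs are equal, or misstate a real one. The confidence interval promised in the analysis plan would be for a ratio of geometric means, not for an amount of money.

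The log step is conditional on skewness, but it will very probably apply. Bed stay is one of the two named cost components, and Section 8.2 expects length of stay to be skewed.

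Two smaller matters belong to the same analysis: whether the cost of the study scan is counted, and whether a comparison of costs alone can answer a cost-effectiveness aim.

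**Working it through.** The plan gives no figure for costs, so there is none to reproduce. The check uses length of stay as a stand-in for cost.

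**Inputs**
- Mean log10 length of stay 2.01, SD 0.36, and a reduction from 103 to 79 hours (Section 8.2).
- 250 participants, so 125 per arm (Section 8.2).
- Secondary threshold p < 0.01 (Section 8.3).
- Assumptions: costs are lognormal with the length-of-stay SD in one arm. The SD in the other arm is varied, because the documents give no cost data.

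**Step 1. Geometric against arithmetic mean.** On the natural-log scale, s = 0.36 × ln 10 = 0.829. Arithmetic mean / geometric mean = exp(s²/2) = exp(0.3436) = 1.41. The control geometric mean is 10^2.01 = 102 h and the arithmetic mean is 102.3 × 1.41 = 144 h. The geometric mean is 1 − 1/1.41 = 29% lower.

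**Step 2. Equal log-scale variances.** Ratio of arithmetic means = ratio of geometric means × exp((s₁² − s₀²)/2), where 1 is the ultrasound arm and 0 the control arm. With s₁ = s₀ both ratios are 79/103 = 0.767, and the null hypotheses coincide. The absolute differences still do not agree: 103 − 79 = 24 h between geometric means, but 24 × 1.41 = 33.8 h between arithmetic means.

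**Step 3. Unequal variances, same geometric-mean ratio of 0.767.** With a control SD of 0.36 and an ultrasound-arm SD of 0.30, 0.33, 0.39 or 0.42, the ratio of mean costs is 0.69, 0.73, 0.81 or 0.87. At an SD of 0.42, for example, a 23% geometric reduction is a 13% reduction in mean cost.

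**Step 4. Rejection rate when mean costs are equal.** Let σ be the second arm's log10 SD. The difference in mean log cost is then d = ½(ln 10)²(0.36² − σ²), with standard error SE = ln 10 × √((0.36² + σ²)/125). For σ = 0.30:
- d = ½ × 5.302 × (0.1296 − 0.0900) = 0.105, a geometric-mean ratio of 1.11.
- SE = 2.3026 × √(0.2196/125) = 0.0965, so d/SE = 1.088.
- Rejection at 0.01 is Φ(1.088 − 2.576) = 6.8%; at 0.05 it is Φ(1.088 − 1.960) = 19%. The opposite tail is negligible.

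The same formulas, keeping the opposite tail where it matters, give the other rows. The simulated values come from 20,000 trials per scenario.

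| SD in second arm (assumed) | d/SE | p < 0.01, formula | p < 0.01, simulated | p < 0.05, formula | p < 0.05, simulated |
|---|---|---|---|---|---|
| 0.36 | 0 | 1.0% | 1.1% | 5.0% | 5.5% |
| 0.34 | 0.364 | 1.5% | 1.5% | 6.5% | 6.4% |
| 0.33 | 0.546 | 2.2% | 2.0% | 8.5% | 8.1% |
| 0.30 | 1.088 | 6.8% | 6.5% | 19% | 19% |

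**Step 5. Is the scan costed?** Section 4.3 counts investigation costs. Section 5.1 lists, among the investigations recorded, "Imaging such as X-ray, CT, MRI, nuclear medicine and ultrasound including echocardiography", which could cover the study scan. Section 5.2 places "Focused Cardiac, Lung and femoral and popliteal vein Ultrasound" in the column for procedures additional to standard care, apart from the row for investigations ordered by the treating team. The synopsis adds that "the researcher will perform a focused cardiac, lung, and femoral and popliteal vein ultrasound", so the scan may generate no hospital charge. No section includes the scan in the cost and none excludes it.

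**The case against.** The strongest defence is that Section 8.2 assumes a common SD on the log scale. If that also holds for costs, the log test and a test of the ratio of mean costs share one null hypothesis, and the error rate is nominal. This stands. The inflated rates above depend on SDs that are assumed, and at 0.34 the inflation is slight. Cost is also a secondary outcome, so p < 0.01 is the relevant threshold; the 19% at 0.05 overstates the risk under the protocol's own rule. Nothing in the plan forbids reporting mean costs as well.

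The defence does not supply the missing estimate. Equal variances rescue the test, not the difference in money.

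A reader might infer that the log test is biased in favour of the ultrasound because it mainly shortens long stays. The documents do not support that. No section predicts such a pattern. Shortening long stays would also lower the ultrasound arm's arithmetic mean, which is not the equal-means scenario. Equal means with a smaller spread under ultrasound imply a higher geometric mean in that arm, so the test would err against it.

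A reader might also infer that the intervention arm is costed without its intervention, always to the ultrasound's advantage. Sections 4.3, 5.1 and 5.2 can be read either way, so only the lack of specification is established. No unit cost is given, so the size of any omission cannot be computed.

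**Conclusion.** The point holds as a mismatch between the stated aim and the committed analysis. The planned test targets the ratio of geometric means; the aim needs the arithmetic mean difference. If costs have the spread of length of stay, the geometric mean lies 29% below the arithmetic mean. With equal mean costs, the false-positive rate at p < 0.01 runs from the nominal 1% at equal SDs to about 6.5% at 0.36 against 0.30. These sizes rest on lognormal costs, the borrowed SD of 0.36 and assumed SDs in the other arm. The mismatch of quantities does not depend on them.

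The costing of the study scan is unspecified, not shown to be omitted. Aim (e) goes further than the analysis, because no effect measure is linked to cost. The primary analysis is unaffected. The change should be made before any economic conclusion is reported.

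**What to change.** - Replace the log-scale t-test for costs by the difference in arithmetic mean cost per patient on untransformed data, with a bootstrap 95% confidence interval. A gamma model with log link, reported as a predicted mean difference, would also serve.
- State in Section 4.3 that the study scan is costed in the intervention arm, and give the unit cost used. Section 7.1 puts scanning at about 15 minutes; the other components need a stated source.
- Name the effect measure to be set against cost, or reword aim (e) as a cost comparison.

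This takes edits to the analysis plan and to Sections 4.2 and 4.3, plus one unit cost. It needs no further patient data and no change in sample size. The price is a wider confidence interval than on the log scale. Counting the scan also adds its unit cost to the intervention arm, if it was not already included.
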